### Study population

#### Eligibility criteria

Participants will be drawn from a population of adult patients who will undergo elective colorectal surgery. Patients with an absolute contraindication for the study medication, such as pregnant women or nursing mothers, patients with a previously diagnosed allergy for the antibiotics in the study medication or patients with myasthenia gravis, are excluded from participation. Inclusion and exclusion criteria are presented in Table 1.

**Table 1 Tab1:** Inclusion and exclusion criteria

Inclusion criteria	Exclusion criteria
Adult patients undergoing elective colorectal surgery	Age < 18 years Legally incapacitated patients Patients who are unable to sign informed consent Patients who have an inability to take medication orally Patients who have undergone abdominal surgery within 30 days before randomization Patients with a documented allergy to colistin or aminoglycoside antibiotics Pregnant women or nursing mothers Patients diagnosed with myasthenia gravis Patients with a pre-existent stoma Patients who previously participated in the PreCaution trial or patients who already received study medication but for whom surgery was postponed for more than 7 days

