### Outcome measures

As a primary composite endpoint, we will investigate the efficacy of Pre-OP on deep SSI and/or mortality within 30 days after surgery. The secondary endpoints including their definitions are summarized in Table 2.

**Table 2 Tab2:** Definition of endpoints

Endpoints	Definitions
Primary composite endpoint	
Cumulative incidence of deep surgical site infection and/or mortality within 30 days after surgery	Deep SSI will be diagnosed according to the CDC criteria for surgical site infections [37]. Deep SSI includes both deep incisional SSI and organ/space SSI
Secondary endpoints	
*30 days after surgery*	
Cumulative incidence of superficial SSI	Superficial and deep SSIs will diagnosed according to the CDC criteria for surgical site infections [37]
Cumulative incidence of deep SSI	
All-cause mortality	
Cumulative incidence of bacteremia	Blood cultures positive for microorganisms
Cumulative incidence of infection with *Clostridium difficile*	Stool sample positive for *C. difficile* toxins
Cumulative incidence of infection with HRE	Clinical cultures positive for ESBL or carbapenemase-producing *Enterobacteriaceae* or *Enterobacteriaceae* resistant to quinolones and/or aminoglycosides [38]
Cumulative incidence of rectal colonization with HRE and colistin resistant species	Rectal swabs positive for HRE or colistin resistant species, measured at baseline and 30 days after surgery
Cumulative incidence of anastomotic leakage	Clinical and/or radiological evidence of leakage requiring surgical or radiological reintervention
Cumulative incidence of re-laparotomy	Reoperation in the abdominal region
In-hospital use of antibiotics	Defined as “days on therapy”
*6 months after surgery*	
All-cause mortality	
Quality of life	Measured with the RAND-36 questionnaire [39]
Length of hospital stay	In days, including all readmissions
Length of ICU stay	In days, including all readmissions
In-hospital costs	

*CDC* Centers for Disease Control and Prevention, *ESBL* extended-spectrum beta-lactamase, *HRE* highly resistant *Enterobacteriaceae*, *ICU* intensive care unit, *SSI* surgical site infection

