^a^The day of surgery is referred to as day 0. The exact time points of the first and second preoperative visits to the outpatient clinic will depend on the local schedules and procedures

^b^Screening and enrollment are performed during visits to the outpatient clinic. These visits are not study-specific and are planned according to the local logistics

^c^The postoperative data collection is performed by assessment of the patient registers. A phone call will be made at around day 30 and month 6 to assess the status of the patient and to remind the patient to perform the rectal swab (day 30) and fill in the questionnaire (month 6)

Patients will be followed until 6 months after surgery to evaluate the development of primary and secondary outcomes. The data on almost all of these outcomes, including infectious complications will be documented as part of daily practice. Thirty days after surgery, the medical records will be assessed to collect data on primary and secondary outcomes and a second rectal swab will be taken by either the patient or by a member of the local study team. Six months after surgery, the medical records will be assessed again to collect additional data on readmissions and length of hospital stay, including admissions to the ICU. Furthermore, patients will receive the second quality-of-life questionnaire. After the questionnaire has been completed and sent back to the study team, the follow-up is completed.

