#### Retention and withdrawal of participants

Patients are free to withdraw from the study at any time, which is in accordance with the Dutch law on medical research on humans. When patients are unwilling to have the rectal swab taken or to fill in the questionnaire, these data will considered to be missing and will be dealt with in data analysis using the appropriate methods.

The intention-to-treat principle will be applied to our primary analysis to deal with poor or non-compliance to the study medication, as this is likely to reflect daily practice. The remainders of study medication will be weighted to estimate the compliance. To enhance the compliance, patients are informed about the bitter taste of the treatment and are advised to take the study medication together with other drinks to mask the taste. Another strategy that will be applied to enhance retention of patients is to call the patients on the two postoperative follow-up moments to remind them about the rectal swab requirement and the questionnaire that will be send to their home address.

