#### Microbiological methods

Clinical cultures will be performed and processed in the local microbiology laboratory of the participating centers according to the routine laboratory procedures. Date of culture, specimen type, species cultured, antimicrobial susceptibility and the production of extended-spectrum beta-lactamase or carbapenemase will be documented. Fecal samples from patients who develop nosocomial diarrhea will be tested for the presence of *Clostridium difficile* toxins, according to routine laboratory procedures and based on the indication by the attending physician.

Rectal swabs will be pre-enriched and subsequently cultured using selective media, aimed at the detection of extended-spectrum beta-lactamase (ESBL)-producing *Enterobacteriaceae* and carbapenem-, tobramycin- and colistin-resistant, Gram-negative bacterial species’ identification and antimicrobial susceptibility testing will be performed for all isolates that grow on either one of the screening agars. Phenotypic ESBL confirmation will be performed with the combination disk diffusion method according to the NVMM guideline on the laboratory detection of highly resistant microorganisms (HRMO).

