#### Adverse events

Pre-OP consists of non-absorbable antibiotics. When taken orally, there is virtually no uptake of antibiotic components in the bloodstream. It is, therefore, expected that the occurrence of systemic side effects is negligible. More importantly, there is extensive experience with non-absorbable antibiotics applied as SDD on ICUs and severe and acute side effects that could apply to the current study have not been reported [27–30]. For this reason, we decided to refrain from an obligatory observation period after intake of the first dose of the study medication and patients can, therefore, take the medication at home. Nevertheless, patients will receive information about severe side effects of this study medication and are instructed to seek medical advice when they might suffer from severe acute side effects. The unblinding protocol can be freely assessed via our website, when deemed necessary. Late side effects, such as the development of antibiotic resistance, have not been described either [31–35]. Nevertheless, the occurrence of side effects and the development of antibiotic resistance will be monitored as secondary endpoints of this study.

All adverse events will be reported to the principle investigator. Serious adverse events (SAEs), serious adverse reactions (SARs) and suspected unexpected serious adverse reactions (SUSARs) will be reported to the sponsor within 24 h after notification of the event. For the SAEs, we decided to only report life-threatening infections with colistin- or tobramycin-resistant bacteria or *C. difficile* colitis within 24 h. Postoperative complications that are known to occur after colorectal surgery and are not directly related to the study medication will be reported to the ethical board in periodic line-listings and not within the 24-h time window.

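### Day-30 resistance colonisation is defined by a rectal swab alone, although patients whose rectum is removed or diverted at the index operation are enrolled

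*Protocol article*

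**What the plan says.** **Who is enrolled.** Table 1 of the protocol article (Eligibility criteria) has one inclusion line: "Adult patients undergoing elective colorectal surgery". The only exclusion that concerns a stoma is "Patients with a pre-existent stoma". Nothing limits the type of resection or a stoma made at the index operation. The Statistical analysis section plans subgroups by surgical procedure and by preoperative radiation of the surgical site, so a mix of operations is expected.

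**How colonisation is measured.** Table 2 (Outcome measures) gives the definition as "Rectal swabs positive for HRE or colistin resistant species, measured at baseline and 30 days after surgery". Study procedures says that at 30 days "a second rectal swab will be taken by either the patient or by a member of the local study team", and the footnote to Table 3 adds a phone reminder to patients to do the swab. Microbiological methods describes the colonisation work-up for this specimen only: "Rectal swabs will be pre-enriched and subsequently cultured using selective media". No alternative specimen is named anywhere in the article.

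**What happens when a swab is absent.** The section on retention and withdrawal covers one cause: "When patients are unwilling to have the rectal swab taken or to fill in the questionnaire, these data will considered to be missing". It then refers to appropriate methods of analysis. The missing-data sentence in Statistical analysis breaks off in the text at hand, so no method can be read from it.

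**What the endpoint is for.** The Adverse events section states that "the occurrence of side effects and the development of antibiotic resistance will be monitored as secondary endpoints of this study". Another Table 2 endpoint, infection with HRE, is read from clinical cultures; its definition begins "Clinical cultures positive for ESBL or carbapenemase-producing" and goes on to quinolone and aminoglycoside resistance. It does not mention colistin.

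**The concern.** The specimen rule does not fit everyone whom the eligibility rule admits. At baseline there is no difficulty, because patients with a stoma are kept out. At day 30 two groups arise from the operation itself:

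- **Rectum removed.** The defined specimen cannot be obtained.
- **Rectum left but diverted or closed off.** The specimen can be obtained, but it comes from bowel that no longer receives faeces. A patient who carries resistant bacteria in the functioning bowel could be scored negative.

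The study drugs are colistin and tobramycin, and selection of resistance is the main late harm that the plan sets out to monitor. Within Table 2, colistin resistance appears in this endpoint and in no other. Lost yield or lost patients here weaken the one planned comparison of carriage between the arms. In a safety comparison, lost power makes a reassuring null result more likely.

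**Working it through.** **1. Figures in the plan.** The article gives no expected rate, power or sample size for colonisation, so there is no stated figure to reproduce for this endpoint. The only sample size is 966 for the primary endpoint (14% against 8.4%, one-sided 2.5%, 80% power). The usual two-proportion formula gives 988 to 994 before any allowance for the interim look, so 966 is 2-3% lower. That is not at issue here. I use it only for the arm size, 966 / 2 = 483.

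**2. Inputs that must be assumed.** The documents do not give:
- s, the share of swabbed patients whose rectum is diverted at day 30;
- q, the yield of a rectal swab in them relative to patients with the bowel in continuity;
- the true carriage rates.

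**3. Diverted rectum.** Let the true carriage be p, the same in diverted and other patients, with no false positives. The observed rate is

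p × [(1 - s) + s × q] = p × [1 - s(1 - q)].

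With equal s and q in both arms, the risk difference is multiplied by the same factor, so it shrinks by s(1 - q):

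| s | q | s(1 - q) |
|---|---|---|
| 10% | 0.5 | 0.10 × 0.5 = 5% |
| 10% | 0.3 | 0.10 × 0.7 = 7% |
| 30% | 0.5 | 0.30 × 0.5 = 15% |
| 30% | 0.3 | 0.30 × 0.7 = 21% |

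The factor cancels in the risk ratio, which stays as it was. The odds ratio hardly moves. With assumed true rates of 10% and 5%, it is (0.10/0.90) / (0.05/0.95) = 2.11. With the factor 0.79 (s = 30%, q = 0.3), it is (0.079/0.921) / (0.0395/0.9605) = 2.09.

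**4. Power, for illustration.** Assumed true carriage 10% against 5%, 483 per arm, two-sided 5%:

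| Case | Observed rates | Risk difference | Power |
|---|---|---|---|
| No loss | 10.0% / 5.0% | 5.0 points | 84% |
| s = 10%, q = 0.75 | 9.75% / 4.88% | 4.9 points | 83% |
| s = 10%, q = 0.5 | 9.5% / 4.75% | 4.75 points | 82% |
| s = 30%, q = 0.5 | 8.5% / 4.25% | 4.25 points | 77% |
| s = 30%, q = 0 | 7.0% / 3.5% | 3.5 points | 68% |

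**5. Rectum removed.** These patients have no result. If they are equally frequent in both arms and their carriage is like that of the others, neither rate is shifted. Only the numbers fall. With 10%, 20% or 30% missing, 434, 386 or 338 per arm remain, and power under the same assumed rates is 80%, 75% or 70%.

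**6. If the loss is not equal across arms.** A stoma can also be made at a reintervention, and anastomotic leakage and re-laparotomy are themselves endpoints that the drug may change. Take q = 0.5, with s = 20% in one arm and 30% in the other, so that the factors are 0.90 and 0.85. If the active arm has the lower share, the observed risk ratio is 0.090 / 0.0425 = 2.12. If it has the higher share, the ratio is 0.085 / 0.045 = 1.89. The true ratio is 2.0, so this component can act in either direction.

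**The case against.** **A reader might infer that resistance at day 30 is measured only by the rectal swab.** That is true of colonisation, not of resistance as a whole. HRE infection is a separate 30-day endpoint from clinical cultures, and its definition covers aminoglycoside resistance. Susceptibility of clinical isolates is documented. Life-threatening infections with colistin- or tobramycin-resistant bacteria fall under 24-hour reporting. None of these needs a rectum, but all need a clinical culture or an infection, so none measures carriage.

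**A reader might infer that every affected patient pulls the comparison towards no difference.** The documents do not support this. No section scores an absent swab as negative. Loss of the rectum depends mainly on the planned operation, and allocation is randomised and blinded. For diverted patients, an equal loss of yield lowers the risk difference and not the risk ratio, and the article fixes no effect measure for this endpoint.

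**A reader might infer that inability would be pooled with refusal.** The article names unwillingness as one cause and is silent on inability. It does not say that the two are combined.

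**The size is assumed.** This stands. No procedure mix, stoma rate or swab yield is given, and pre-enrichment with selective media may keep q higher than the values used here.

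**An article condenses the full protocol.** Swab instructions and the case report form are not shown and may deal with stoma patients. That would settle the practice, but Table 2 states the specimen as part of the endpoint definition, and the other sections repeat it. Any such instruction would then conflict with the published definition.

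**Conclusion.** The point holds as a mismatch between the eligibility rule and the endpoint definition. As written, the day-30 rule yields no result in patients without a rectum and an out-of-stream sample in patients with a diverted one.

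In the first group the cost is precision and representativeness, without bias in itself. In the second, carriage may be missed. Absolute rates, the risk difference and power then fall, while the risk ratio holds if the loss is equal across arms. The attenuation of the risk difference is s(1 - q), 5-21% for assumed s of 10-30% and q of 0.3-0.5. It cannot be derived from the documents and could be smaller.

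The consequence is confined to one secondary endpoint, but that is the only colonisation endpoint and the only one in Table 2 that covers resistance to colistin. The primary endpoint and the sample size of 966 are not affected.

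**What to change.** - In Table 2 and the sampling instruction, define the day-30 specimen as a rectal swab when the bowel is in continuity and a swab of stoma output otherwise, processed on the same selective media.
- Record the sample site and the reason for any absent swab (impossible or refused), and report both by arm.
- Add a sensitivity analysis limited to patients with a rectal swab at both time points. It conditions on what happened at and after surgery, so it supports the main comparison and does not replace it.

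**Cost.** One line of instruction and short form entries for site and reason, with the same swab, media and time point. The downside is that the sample site differs between baseline and day 30 in patients with a new stoma, which the sensitivity analysis addresses in part. Recruitment began in April 2017, so the rule would apply only to day-30 samples still to be taken. Earlier samples would have to be classified from the operation records where these allow it.

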### Treatment of subjects

#### Intervention

All patients will receive the study medication as part of the intervention. The intervention can either be treatment with active medication (Pre-OP) or a placebo. Pre-OP is a transparent solution that consists of two antibiotic components: colistin sulphate (20 mg/mL) and tobramycin (16 mg/mL). Placebos are manufactured without the active antibiotic components. The placebo solutions contain flavoring additives and colorants to mimic the taste and color of Pre-OP. All patients will receive perioperative intravenously administered prophylaxis according to the national infection prevention guidelines [26].

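### The rectal colonization endpoint does not separate acquired colistin resistance from carriage of naturally colistin-resistant Gram-negatives, and pools both with HRE

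*Protocol article*

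**What the plan says.** Table 2 (Outcome measures) labels the endpoint "Cumulative incidence of rectal colonization with HRE and colistin resistant species" and defines it as "Rectal swabs positive for HRE or colistin resistant species, measured at baseline and 30 days after surgery". The label joins the two parts with *and*; the definition, and the matching row of Table 3, use *or*. The HRE infection row of the same table spells HRE out: producers of ESBL or carbapenemase, or Enterobacteriaceae "resistant to quinolones and/or aminoglycosides". The colistin part has no comparable specification.

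Microbiological methods says the swabs are grown on selective media aimed at ESBL producers "and carbapenem-, tobramycin- and colistin-resistant, Gram-negative bacterial species". It then says "identification and antimicrobial susceptibility testing will be performed for all isolates that grow on either one of the screening agars". It makes no exception for species with natural resistance.

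On timing, the first swab is taken at the enrollment visit, before study medication, and at day 30 "a second rectal swab will be taken by either the patient or by a member of the local study team" (Study procedures). On purpose, the Adverse events section says "the occurrence of side effects and the development of antibiotic resistance will be monitored as secondary endpoints of this study". Under Intervention, colistin and tobramycin are in the active solution only.

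**The concern.** Some Gram-negatives found in the gut, *Proteus* for example, are colistin resistant by nature. The article does not say this; it is general microbiology, and the point depends on it. Read literally, a patient carrying ordinary *Proteus* and a patient carrying an *E. coli* that has become colistin resistant receive the same value, and so does a patient carrying an ESBL producer.

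Among the Table 2 endpoints this is the only one whose definition includes colistin resistance, because the HRE infection definition does not mention it. The result could mislead in two directions:

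- **Dilution.** Background carriage that is equal in both arms could hide a real rise in acquired colistin resistance.
- **Relabelling.** Colistin is given in one arm only. If it favours naturally resistant species, the arms will differ, and the difference could be reported as resistance development although nothing was acquired.

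**Working it through.** **Textual check.** The article states no figure for this endpoint, so there is none to reproduce.

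1. Table 2 fixes the rule: HRE, or any colistin-resistant species, makes the swab positive.
2. Microbiological methods does not narrow the rule. The media target colistin-resistant Gram-negatives in general.
3. The same section provides species and susceptibility for every isolate that grows on a screening agar. The data can therefore separate the groups; only the endpoint definition does not.

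**Illustration of dilution.** Every rate here is an assumption.

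- Let *a* be acquired colistin resistance at day 30, *q* naturally resistant carriage and *h* HRE carriage, taken as independent. Set *a* = 1% (placebo) vs 4% (Pre-OP), with *q* and *h* equal in both arms.
- Use 400 evaluable swabs per arm, below the 966/2 = 483 randomized per arm, to allow for missing swabs.
- Observed positivity: p = 1 − (1−a)(1−q)(1−h).
- Power, two-sided 5%: Φ[(|p₁−p₀| − 1.96·se₀)/se₁], with se₀ from the pooled proportion and se₁ from the two separate proportions.

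Worked case, *q* = 10% and *h* = 0:

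- p₀ = 1 − 0.99×0.90 = 0.109; p₁ = 1 − 0.96×0.90 = 0.136; difference 0.027; pooled proportion 0.1225.
- se₀ = √(0.1225×0.8775×2/400) = 0.0232.
- se₁ = √[(0.109×0.891 + 0.136×0.864)/400] = 0.0232.
- Power = Φ[(0.027 − 0.0454)/0.0232] ≈ 21%.

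| q | h | Placebo | Pre-OP | Risk ratio | Power |
|---|---|---|---|---|---|
| 0 | 0 | 1.0% | 4.0% | 4.00 | 78% |
| 2% | 0 | 3.0% | 5.9% | 1.99 | 52% |
| 5% | 0 | 6.0% | 8.8% | 1.48 | 34% |
| 10% | 0 | 10.9% | 13.6% | 1.25 | 21% |
| 20% | 0 | 20.8% | 23.2% | 1.12 | 13% |
| 0 | 10% | 10.9% | 13.6% | 1.25 | 21% |
| 5% | 10% | 15.4% | 17.9% | 1.17 | 16% |

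The risk difference barely shrinks (3.0 to 2.7 points in the worked case). Power is lost because the background raises the variance. The last two rows show that pooling with HRE does the same damage: at 10% HRE, adding 5% natural carriage lowers power only from 21% to 16%.

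With larger assumed effects the pattern is the same. At 483 per arm, *h* = 0 and *a* = 5% vs 10%, power is 84% at *q* = 0, then 62%, 47% and 29% at *q* = 5%, 10% and 20%.

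**Illustration of relabelling.** Now let *a* (acquired resistance or HRE) be 5% in both arms, with natural carriage 10% vs 20% and 483 per arm.

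- p₀ = 1 − 0.95×0.90 = 14.5%; p₁ = 1 − 0.95×0.80 = 24.0%; risk ratio 1.66.
- The probability of a significant difference is 96%, although no resistance was acquired. With natural carriage 10% vs 15% it is 50%.

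**The case against.** A reader might infer that the endpoint fails to measure resistance development at all, or that it is the trial's main resistance safety measure. The documents support neither. The HRE part does not depend on colistin and covers aminoglycoside resistance, hence the tobramycin component. The Adverse events section speaks of secondary endpoints in the plural and names none; infection with HRE is also in Table 2, and life-threatening infections with colistin- or tobramycin-resistant bacteria are reported within 24 hours.

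Four further objections have weight:

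- **Colonization is what the label says.** Overgrowth of naturally resistant flora under colistin is a true ecological effect, and the Discussion names opportunistic infection as a concern alongside resistance. This stands, and is a reason to report such carriage separately rather than drop it. It does not justify giving it the same value as acquired resistance.
- **Placebo control and a baseline swab.** They protect the comparison between arms, not its meaning. A naturally resistant species first detected at day 30 still counts.
- **The magnitude is assumed.** This stands. The drop in power cannot be credited to natural resistance alone, since merging with HRE can produce it too. That supports separating all three groups.
- **The full protocol or SAP may define the term, and nothing says only one binary result will be reported.** Possibly so. But Table 2 is headed as the definition of endpoints, and what it states is unrestricted.

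**Conclusion.** The point holds for the colistin component and for its pooling with HRE. As defined, a positive swab may mean acquired colistin resistance, naturally resistant flora or HRE, and a difference between arms, or its absence, cannot be attributed to any one of them.

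The size cannot be set from the documents. The power figures above are illustrations under assumed carriage rates, independence of the components and assumed swab numbers, and should be labelled so wherever they are used. The conclusion also rests on the general microbiological fact that some gut Gram-negatives are naturally colistin resistant. This is a secondary endpoint: the HRE component as such, the primary endpoint and the sample size are untouched.

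**What to change.** Before unblinding, amend the definition in Table 2 and the matching analysis so that the following are reported by arm, at baseline and at day 30:

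- (a) rectal carriage of HRE;
- (b) colistin resistance in species that are normally colistin susceptible, named as the colistin resistance-development endpoint;
- (c) carriage of naturally colistin-resistant Gram-negatives, named as a shift in flora.

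List the species assigned to (b) and (c) in advance, so that none is moved after results are known.

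The cost is three reported rows instead of one. No new swabs or tests are needed, because identification and susceptibility testing are already planned for all isolates growing on a screening agar.

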### Assessment and follow-up

#### Study procedures

The study procedures are listed in Table 3. The preoperative study procedures will take place during visits to the outpatient clinic. These visits will be routinely scheduled and will not be planned as study-specific procedures. During the first visit, the trial will be explained and patients will receive an information letter. Informed consent will be signed during a second preoperative visit. During this visit, the study medication will be provided along with instructions for use and a study diary. Furthermore, the first rectal swab will be taken and patients will receive the first quality-of-life questionnaire. The study diary will be used to document the intake of study medication and to report potential side effects due to the study medication. Patients will take the study medication according to the instructions during the 3 days prior to surgery. The bottles with remainders of study medication will be collected at hospital admission and will be weighted to estimate treatment adherence. The study diaries will also be collected at admission.

**Table 3 Tab3:** Study flow

	Study period							
	Screening^b^	Enrollment^b^	Intervention			Follow-up and postoperative procedures^c^		
			day					
Time point^a^	~ − 2 weeks	~ − 2 weeks to day − 4	−3	−2	−1	Day 0	Day 30	Month 6
Patient recruitment	X							
Eligibility screening		X						
Informed consent		X						
Allocation		X						
Rectal swab		X					X	
Intake study medication			X	X	X			
Surgery						X		
Estimation of compliance			X	X	X			
Patient characteristics	X	X						
Surgical characteristics						X		
Primary endpoint Deep SSI and/or mortality							X	
Secondary endpoints								
Superficial SSI							X	
Anastomotic leakage							X	
Re-laparotomy							X	
Bacteremia							X	
Rectal colonization with HRE or colistin resistant species							X	
Infection with HRE							X	
Infection with *Clostridium difficile*							X	
In-hospital antibiotic use							X	
Length of hospital stay								X
Length of ICU stay								X
All-cause mortality							X	X
In-hospital costs								X
Quality of life		X						X
Adverse events		X	X	X	X	X	X	X
Serious adverse events		X	X	X	X	X	X	X
SUSARs/SARs			X	X	X	X		

*HRE* highly resistant *Enterobacteriaceae*, *ICU* intensive care unit, *SAR* serious adverse reaction*, SSI* surgical site infection, *SUSAR* serious unexpected adverse reaction

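### Rectal carriage is defined as one pooled positive/negative status, so a rise in resistance to the study drugs could be diluted or offset by a fall in other resistant carriage

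*Protocol article*

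**What the plan says.** - **Endpoint.** Table 2 (Outcome measures) has one row for carriage, titled "Cumulative incidence of rectal colonization with HRE and colistin resistant species". Its definition cell reads "Rectal swabs positive for HRE or colistin resistant species, measured at baseline and 30 days after surgery". The schedule in Table 3 (Study procedures) again has one row: "Rectal colonization with HRE or colistin resistant species".
- **Meaning of HRE.** The carriage row does not define HRE. The row on HRE infection in the same table does: ESBL or carbapenemase producers, "or *Enterobacteriaceae* resistant to quinolones and/or aminoglycosides".
- **Study drugs.** Under Intervention, the active solution contains colistin sulphate and tobramycin.
- **Laboratory work.** Microbiological methods describes selective media aimed at ESBL producers and at carbapenem, tobramycin and colistin resistance, and states that "identification and antimicrobial susceptibility testing will be performed for all isolates that grow on either one of the screening agars".
- **Purpose.** The Adverse events section says that "the occurrence of side effects and the development of antibiotic resistance will be monitored as secondary endpoints of this study".
- **Contrast.** For the primary composite, the Discussion promises that mortality and deep SSI will also be analyzed separately. Nothing comparable is said for carriage.

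**The concern.** The two parts of the carriage outcome need not move together. The Discussion states that the intervention is meant to decontaminate the digestive tract, so it could reduce HRE that remain susceptible to a study drug. The same exposure could select for organisms resistant to colistin or tobramycin. A swab status joined by a single *or* adds the two and shows only the net change.

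Tobramycin resistance is harder still to see. In Enterobacteriaceae it sits inside HRE, together with ESBL, carbapenemase and quinolone resistance. In other Gram-negatives it has no place in the outcome unless the isolate is also colistin-resistant, although the culture method appears to look for it.

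At stake is the trial's conclusion on whether its own drugs select for resistance. The primary efficacy result is not affected.

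**Working it through.** **The plan's own figure.** There is none to reproduce: the documents give no rate, power or sample size for carriage. The total of 966 under Sample size concerns the primary endpoint only. It caps the swabs at 966 / 2 = 483 per arm.

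**Inputs, all assumed.** 400 swabs per arm (some missing swabs), two-sided 5%, HRE and colistin resistance independent. Colistin-resistant carriage is 2% on placebo and 6% on Pre-OP. HRE carriage is 10% on placebo, and 10% or 7% on Pre-OP.

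**Formulas.** Pooled rate = 1 − (1 − HRE)(1 − colistin-resistant). With difference d, s0 the standard error under equal rates and s1 the standard error under the two rates, power = Φ((|d| − 1.96·s0)/s1), plus the opposite tail where that is not negligible.

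1. *Colistin resistance alone, 2% v 6%.* s0 = √(2 × 0.04 × 0.96/400) = 0.01386. s1 = √((0.0196 + 0.0564)/400) = 0.01378. (0.04 − 0.02716)/0.01378 = 0.93, so power is **82%**.
2. *Pooled, HRE unchanged at 10%.* 1 − 0.90 × 0.98 = 11.8%; 1 − 0.90 × 0.94 = 15.4%. d = 0.036, s0 ≈ s1 ≈ 0.0242. (0.036 − 0.0475)/0.0242 = −0.48, so power is **32%**. This is pure dilution; nothing has been offset.
3. *Pooled, HRE 10% to 7%.* 1 − 0.93 × 0.94 = 12.6%, against 11.8%. d = 0.0078, s ≈ 0.0231. The two tails are 5.2% and 1.1%, so power is **about 6%**.

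**Sensitivity to the assumptions (400 per arm unless stated).**

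| Assumed change, placebo to Pre-OP | Pooled rates | Pooled test | Colistin resistance alone |
|---|---|---|---|
| HRE 15% to 10.5%, colistin-resistant 2% to 6% | 16.7% v 15.9% | about 6% | 82% |
| HRE 20% to 12%, colistin-resistant 2% to 6% | 21.6% v 17.3% | about 34%, almost all towards apparent benefit | 82% |
| HRE 10% unchanged, colistin-resistant 2% to 3% | 11.8% v 12.7% | about 7% | about 15% |
| 483 per arm: colistin-susceptible HRE 10% to 6%, colistin-resistant 2% to 6% | 12% v 12% | difference 0 | 89% |
| 483 per arm: colistin-susceptible HRE 10% unchanged, colistin-resistant 2% to 6% | 12% v 16% | 43% | 89% |

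The last two rows drop independence: they add colistin-susceptible HRE to all colistin-resistant carriage. Dilution and masking do not depend on the independence assumption. The third row shows the limit: for a small rise, separation recovers little.

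**The case against.** **A single pooled test is not stated outright.** The row title joins the two groups with *and*, so the row can be read as two organism groups listed together. Only the primary endpoint is called composite, and Statistical analysis gives a general list of tests for secondary outcomes. This stands as far as it goes. A reader might infer that a resistance harm would necessarily be reported as no difference; the documents do not support that. Susceptibility is tested on every isolate that grows, nothing rules out a comparison by drug, and an analysis plan not shown may provide one. Still, the definition cell and Table 3 both use *or*. The point concerns a definition that is stated, not a detail left out.

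**Clearance may not count.** If cumulative incidence with a baseline swab means new acquisition, clearing HRE already carried at baseline does not enter the outcome. Only prevented acquisition could then offset a rise, after a 3-day preoperative course and at a day-30 swab. The documents do not say how the baseline swab is used. Offsetting is less plausible under that reading, but dilution needs no fall in HRE.

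**The rates are assumed.** This is correct. Cancellation needs opposite shifts of similar size, and nothing in the documents shows that these would occur.

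**Resistance has other routes to notice.** Infection with HRE is a separate endpoint, susceptibility of clinical cultures is recorded, and life-threatening infections with colistin- or tobramycin-resistant bacteria are reported within 24 h. These routes concern clinical infection and do not replace a comparison of carriage between arms.

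**Conclusion.** The point holds as a weakness in a stated definition. The only carriage endpoint pools resistance to the study drugs with other resistance, leaves some tobramycin-resistant Gram-negatives out, and comes with no commitment to analyze its parts. A rise in study-drug resistance could be diluted or offset in it; the documents do not show that it would be.

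Under the stated assumptions, pooling lowers the power to see colistin resistance go from 2% to 6% from 82% to 32% with HRE unchanged at 10%, and to about 6% if HRE falls from 10% to 7%. These figures illustrate the mechanism and do not forecast the trial's result. For a rise from 2% to 3% the trial would have little power under either definition. The change is worth making because it is cheap and because the protocol assigns the monitoring of resistance to its secondary endpoints.

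**What to change.** In Table 2, replace the pooled row with separate day-30 secondary outcomes, each compared by arm, and align Table 3:

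1. colonization with colistin-resistant Gram-negatives;
2. colonization with tobramycin-resistant Gram-negatives, including those outside Enterobacteriaceae;
3. colonization with ESBL- or carbapenemase-producing Enterobacteriaceae.

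Base the conclusion on resistance selection on (1) and (2), and keep the pooled figure as descriptive. State in the same place how the baseline swab enters, so that all three outcomes use one rule.

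The cost is wording, plus two or three secondary comparisons instead of one. The selective cultures and susceptibility tests are already planned, so no new samples or cultures are needed. No dose or clinical rule is involved.
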